## Photobiomodulation protocol

With regard to the photobiomodulation protocols, the articles of interest were identified through a bibliographic survey of titles and abstracts. The selected articles were analyzed and used for the establishment of the treatment protocol (TABLE 1).

Table1

| PARAMETER         | UNIDADE            | SPINAL
CORD | SUBLINGUAL | ARTÉRIA
RADIAL |
|-------------------|--------------------|----------------|------------|-------------------|
| CENTER WAVELENGTH | nm                 | 808            | 808        | 808               |
| DIAMETRO          | cm                 | 0,4            | 0,4        | 0,4               |
| AREA              | Cm     | 0,1256         | 0,1256     | 0,1256            |
| IRRADIANCIA       | (W/cm  | 1433           | 287        | 287               |
| TIME              | s                  | 1800           | 360        | 360               |
| ENERG             | J                  | 179,9848       | 36,0472    | 36,0472           |

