## **Treatment**

The participant will be placed on an examining table in a comfortable position. Both the operator and participant will use eye protection. Transcutaneous irradiation of the spinal cord will be performed on segments corresponding to the nerve roots of the lumbosacral plexus (T12-S5) and cervicothoracic plexus (C5-T1-2). Twenty points will be irradiated for 90seconds (total treatment time: 1800seconds). In the group submitted to sublingual irradiation, disposable plastic wrap will cover the application pen for the purposes of hygiene, (total treatment time: 360seconds). In the group submitted photobiomodulation on the skin in the region of the radial (total treatment time: 360seconds). The treatment will be performed twice a week totaling 24 consecutive weeks and after 3 months of treatment the patients will be submitted to reassessment of all complementary tests that have been requested, cytokines, nitric oxide, and EDSS.

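### In Table 1 the irradiance row (1433 and 287 W/cm²) contradicts the table's own area, time and energy rows by factors of 1800 and 360; the pattern suggests a mislabelled row

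*Protocol*

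**What the plan says.** Table 1 gives the optical parameters for the three irradiation sites (decimal commas in the original):

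- Beam diameter: "DIAMETRO | cm | 0,4 | 0,4 | 0,4".
- Beam area in cm²: "0,1256 | 0,1256 | 0,1256".
- Irradiance: "IRRADIANCIA | (W/cm 2 | 1433" for the spinal site, then 287 for the sublingual and the radial site.
- Time: 1800 s, 360 s and 360 s.
- Energy in J: "179,9848 | 36,0472 | 36,0472".

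The table has no row for radiant power and none for energy per area.

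The Treatment section repeats the times. For the spinal site: "Twenty points will be irradiated for 90seconds (total treatment time: 1800seconds". For the sublingual site: "disposable plastic wrap will cover the application pen for the purposes of hygiene, (total treatment time: 360seconds". For the radial site: "photobiomodulation on the skin in the region of the radial (total treatment time: 360seconds". It gives the number of points for the spinal site only. It states no power, irradiance or energy.

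**The concern.** Irradiance is power per area, so irradiance, area, time and energy are tied together by one equation. Any three of them fix the fourth. Here the four rows do not satisfy the equation in any column.

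This matters because irradiation is the intervention under test, active against sham at three sites, and Table 1 is the only place in the protocol that states its optical output. Someone preparing the equipment, or a group repeating the study, cannot tell from the document which row governs. The row also bears on how results are compared between sites. As printed, the spinal arm appears to receive five times the irradiance of the other two active arms. The energy and time rows say instead that the irradiance is the same and only the total time is longer.

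**Working it through.** **Inputs.** From Table 1: diameter 0.4 cm, area A = 0.1256 cm², row labelled irradiance I = 1433 / 287 / 287, time t = 1800 / 360 / 360 s, energy E = 179.9848 / 36.0472 / 36.0472 J. From the Treatment section: 20 spinal points of 90 s each, and total times of 1800, 360 and 360 s.

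**Step 1: the rows that agree.** Area = π × (0.4/2)² = 0.1257 cm², or 0.1256 with π taken as 3.14. Time: 20 × 90 = 1800 s for the spinal site, and 360 s in both places for the other two. Diameter, area and time are consistent.

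**Step 2: the energy from the printed irradiance, E = I × A × t.**

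- Spinal: 1433 × 0.1256 × 1800 = 323,973 J, against 179.9848 J stated. Ratio 1800.
- Sublingual and radial: 287 × 0.1256 × 360 = 12,977 J, against 36.0472 J stated. Ratio 360.

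Each ratio equals the treatment time in seconds.

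**Step 3: other readings of the row.**

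- As mW/cm²: 323,973/1000 = 324 J and 12,977/1000 = 13.0 J. Neither matches the stated energies.
- As J/cm², so that E = value × A with no time factor: 1433 × 0.1256 = 179.9848 J and 287 × 0.1256 = 36.0472 J. Both match to all four decimals.

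Of the readings tried, only the last reproduces the energy row.

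**Step 4: what each pair of rows implies.**

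| Quantity | Spinal | Sublingual, radial |
|---|---|---|
| Power from printed irradiance, I × A | 180 W | 36 W |
| Power from energy and time, E / t | 0.0999916 W | 0.1001311 W |
| Irradiance from energy, area and time, E / (A × t) | 0.796 W/cm² | 0.797 W/cm² |

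The printed irradiances differ between sites by 1433/287 = 4.99. The implied irradiances are practically equal.

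**Step 5: spinal points, only if the row is read as J/cm².** The spinal energy is then a total over twenty points divided by the area of one spot. From the table's own energy, each 90 s point would receive 179.9848/20 = 9.0 J, and 8.99924/0.1256 = 71.65 J/cm². The printed 1433 is 20 × 71.65. The same calculation cannot be done for the other two sites, because the protocol does not give their number of points.

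**The case against.** The best defence is that this is one bad label in an otherwise coherent table. Diameter agrees with area, the times agree with the Treatment section, and energy, area and time lead to one setting of about 0.10 W at all three sites. The unit cell has an unclosed bracket, which fits a slip in preparing the table. This stands, and it limits the point in four ways.

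- A reader might infer that the treatment cannot be delivered or reproduced at all. The document does not support that, since a consistent setting can be inferred from three of the four rows. What remains is that the setting has to be inferred and nothing in the protocol confirms it.
- A reader might infer that a device is set wrongly, or that participants are exposed at the printed irradiance. The protocol names no device and does not say that irradiance is what the operator sets. It describes ethics submission as still to come, so no treatment session is shown either. Calling the irradiance row the wrong one would also presuppose that the energy row is right.
- A reader might take Table 1 as the only definition of the intervention. The Treatment section also defines it, through anatomical segments, spinal points, times and frequency. Table 1 is alone only in stating the optical output.
- A reader might count the twentyfold difference in Step 5 as a second contradiction. It arises only once the row is re-read as J/cm². The table does not present 1433 as a per-point value, and its time row is also a session total.

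The defence does not remove the conflict. The row's name and its unit both say irradiance, a lost prefix does not repair it, and the Treatment section gives no figure that decides between the rows. An exact match to four decimals also rules out a digit lost in reading the PDF.

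**Conclusion.** The contradiction is established from the protocol's own figures. The irradiance row conflicts with the area, time and energy rows 1800-fold at the spinal site and 360-fold at the sublingual and radial sites. The second factor is well short of three orders of magnitude. The result rests only on the definition of irradiance as power per area and on the printed values.

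That the row is really energy per area is a likely explanation, because both products match exactly, but it remains an inference. So does the figure of about 0.10 W and 0.80 W/cm² at each site, which assumes that the energy, area and time rows are the intended ones. The per-point spinal figures of 9.0 J and 71.65 J/cm² depend on the same assumption and on equal delivery over the twenty points.

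The apparent fivefold difference in irradiance between the spinal arm and the others follows from the printed row and is not supported by the energy and time rows. Which figures are intended is for the clinical and device team to say.

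**What to change.** Reconcile the irradiance, area, time and energy rows of Table 1 with each other and with the points and times in the Treatment section. For each site, report as separate, correctly labelled rows:

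- radiant power (W);
- irradiance (W/cm²);
- number of points and time per point (s);
- energy per point (J) and energy per area per point (J/cm²);
- total energy per session (J).

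Give the number of points for the sublingual and radial sites in the Treatment section, so that per-point and total quantities can be told apart everywhere. The clinical and device team should confirm the intended values against the equipment specification before the table is reissued.

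The cost is the correction of one table, one matching sentence for each of two sites and a check of the figures. Sample size, randomisation and analysis are not affected.

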## Statistical analysis

The data will be tabulated and treated using the SPSS 20.0 for Windows. Descriptive statistics will be performed. The chi-square test and Fisher's exact test will be used to test associations with the categorical variables. The Student's t-test will be used and Pearson's correlation coefficients will be calculated for the analysis of correlations among the continuous variables. The level of significance will be set at 95% ( $p < 0.05$ ).

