# **Effect of photobiomodulation treatment in the sublingual, radial artery region, and along the spinal column in individuals with multiple sclerosis: Protocol for a randomized, controlled, double-blind, clinical trial**

## **Abstract**

**Background:** Multiple sclerosis (MS) is an autoimmune disease, for which the forms of treatment are medication and rehabilitation. However, *in vitro* and *in vivo* studies have demonstrated that photobiomodulation can be an effective treatment modality for inflammatory diseases, including MS. Photobiomodulation has a broad range of benefits, such as the avoidance of cell and tissue death, the stimulation of healing and injury repair, reductions in pain, edema and inflammation, cell proliferation and even apoptosis. The outcomes of photobiomodulation include the regeneration of cells, the stimulation of the growth of Schwann cells, a reduction in spasticity, functional improvements, a reduction in nitric oxide levels and the upregulation of the cytokine IL10, demonstrating that this therapeutic modality can offer neuro-protection.

**Methods:** A randomized, controlled, double-blind, clinical trial is proposed. The patients will be divided into 6 groups. Groups 1 and 2 will receive sham and active photobiomodulation in the sublingual region, respectively. Groups 3 and 4 will receive sham and active photobiomodulation along the spinal cord, respectively. Group 5 will receive placebo treatment with photobiomodulation on the skin in the region of the radial artery with a specific bracelet. Group 6 will be treated with photobiomodulation on the skin in the region of the radial artery.

**Discussion:** Treatment for MS is directed at the immune response and slowing the progression of the disease. This is one of the first clinical trials involving photobiomodulation in the sublingual region and along the spinal cord, which could help establish a promising new form of non-pharmacological treatment for autoimmune diseases. This is one of the first clinical trials with sublingual photobiomodulation and along

the spinal cord that could help establish a new form of promising treatment of the disease associated with pharmacological treatment.

**Key words:** Low-level laser therapy, photobiomodulation, multiple sclerosis, oxidative stress, physical therapy.

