### **Recruitment and randomization**

Patients will be recruited from the Integrated Health Clinic of University (Vergueiro, Memorial and Vila Maria campuses). Patients with a diagnosis of MS will be screened for the eligibility criteria through telephone interviews. Selected individuals with a signed statement of informed consent will be randomized. Randomization will be performed in blocks. Groups 1 and 2 will receive sham and active photobiomodulation in the sublingual region, respectively. Groups 3 and 4 will receive sham and active photobiomodulation along the spinal cord, respectively. Group 5 will receive placebo treatment with photobiomodulation on the skin in the region of the radial artery with a specific bracelet. Group 6 will be treated with photobiomodulation on the skin in the region of the radial artery. The participants will not be deprived of any medication for the treatment of the

base condition. Randomization will be stratified by clinic using block allocation tables to ensure equal proportions in the distribution of treatments. The participants and evaluator will be blinded to the allocation.

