## **Evaluations**

### **EDSS**

The participants will be evaluated before and after treatment using the Expanded Disability Status Scale administered by a physiotherapist (approximate application time: 15 minutes).

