## Sample calculation

The sample size was calculated to ensure a 95% test power. It was determined that with 32 individuals and an effect size of 0.8, the test power would be 0.9566, thereby maintaining the significance level at  $\alpha = 0.05$  (Figure 1).

[figure not shown]

Figure 1

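### The Student's t-test is left undefined and no named method uses baseline or clinic; one six-arm baseline-adjusted model is a cheap improvement whose gain depends on an unstated correlation

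*Protocol*

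**What the plan says.** - **Method.** The Protocol's Statistical analysis section names chi-square and Fisher's exact tests for categorical variables. For continuous ones it says "The Student's t-test will be used and Pearson's correlation coefficients will be calculated". No other method for continuous outcomes is named.
- **Arms.** The Abstract says "The patients will be divided into 6 groups". These are three sham/active pairs: sublingual, spinal and radial artery.
- **Strata.** Recruitment and randomization says "Randomization will be stratified by clinic using block allocation tables to ensure equal proportions in the distribution of treatments", and lists three campuses.
- **Repeated measures.** For EDSS, "The participants will be evaluated before and after treatment". The blood collection section has IL-10, TNF-alpha and nitric oxide drawn after the diagnostic consultation. The Treatment section has cytokines, nitric oxide and EDSS reassessed later.
- **Size.** Sample calculation says "It was determined that with 32 individuals and an effect size of 0.8, the test power would be 0.9566". It names no test, does not split the 32 by arm, and does not say what kind of effect size 0.8 is.

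**The concern.** A Student's t-test compares two means, or one mean of paired differences. The sentence does not say which, on which quantity, or between which arms, so it allows at least three analyses: final values between arms, changes between arms, or before-after within each arm. The first two are valid under randomisation but differ in precision, depending on how strongly baseline predicts follow-up. The third does not compare active with sham: drift or regression to the mean could be credited to the device.

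None of the three accounts for the clinic strata. The two between-arm readings also estimate the residual variance from two arms at a time, when six could share it. If the arms hold only 5 or 6 patients, both precision and degrees of freedom are scarce.

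**Working it through.** **Inputs from the Protocol:** six arms, equal allocation, three campuses (2 clinic terms if each is a stratum), 32 individuals, effect size 0.8, alpha 0.05.

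**Assumed here:** two-sided test; 0.8 read as a standardised mean difference d for one active-sham pair; 32 read either as the total (32/6 = 5.33 per arm) or as one pair (16 per arm); r = 0.2, 0.5 or 0.7; no clinic effect.

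**Step 1, the plan's own figure.** A one-way ANOVA with four groups, N = 32 and Cohen's f = 0.8 has noncentrality 32 × 0.8² = 20.48 on 3 and 28 df. Its power is 0.9566, the stated value. With six groups (5 and 26 df) it is 0.903. A two-sample t-test with d = 0.8 and 16 per arm gives 0.591. So the stated power does not describe an active-sham t-test.

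**Step 2, power for one contrast (noncentral t, n per arm).**
- t-test on final values: noncentrality d√(n/2), df 2n − 2.
- t-test on changes: d√(n/2) / √(2(1 − r)), same df.
- Six-arm model: d√(n/2) / √(1 − r²), df = N − 6 − 1 − 2, that is 32 − 9 = 23 or 96 − 9 = 87.

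Example, n = 5.33 and r = 0.5: the t-test has noncentrality 0.8 × √2.667 = 1.306 on 8.67 df, power 0.214. The model has 1.306/√0.75 = 1.508 on 23 df, power 0.304.

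| n per arm | r | t, final values | t, changes | six-arm model |
|---|---|---|---|---|
| 5.33 | 0.2 | 0.21 | 0.15 | 0.25 |
| 5.33 | 0.5 | 0.21 | 0.21 | 0.30 |
| 5.33 | 0.7 | 0.21 | 0.32 | 0.42 |
| 16 | 0.2 | 0.59 | 0.41 | 0.63 |
| 16 | 0.5 | 0.59 | 0.59 | 0.73 |
| 16 | 0.7 | 0.59 | 0.81 | 0.88 |

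At r = 0 the model gives 0.24 against 0.21, and 0.61 against 0.59. That small difference comes from pooling the variance over six arms.

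**Step 3, check by simulation.** The formula ignores the cost of estimating the slope and clinic terms. For a 5 v 5 pair in a trial of 32, simulation of the model gives about 0.23, 0.27 to 0.28 and 0.37 to 0.39 at r = 0.2, 0.5 and 0.7, against about 0.20 for the t-test on final values.

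**Step 4, the within-arm reading.** Suppose there is no device effect and every arm drifts by 0.5 SD of change (assumed). A paired t-test with n patients has noncentrality 0.5√n on n − 1 df.
- n = 5: noncentrality 1.118, P(significant) = 0.141. Active significant and sham not: 0.141 × 0.859 = 0.12.
- n = 16: noncentrality 2.0, P = 0.465. Active significant and sham not: 0.465 × 0.535 = 0.25.

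A two-sided 0.05 test between the arms would favour active in 2.5% of null comparisons.

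**The case against.** **The plan does not say that it discards baseline.** A reader might infer that the protocol prescribes separate t-tests on final values and ignores the baseline. The text does not support that: a change-score or paired test fits the same sentence and uses baseline. What it shows is an undefined comparison, and no named method that adjusts for baseline or clinic. This objection stands.

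**Covariates and contrasts belong in the SAP.** An SAP may exist, and the absence of such detail from a protocol is not itself a defect. This stands in part. But the protocol does commit to a method, and a t-test cannot hold six arms, a baseline covariate and clinic. If an SAP specifies a model, the two documents need to agree.

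**The gain can be made to look large.** At a true difference of 1.6 SD and 5.33 per arm, power goes from 0.64 to 0.82 or 0.94 at r = 0.5 or 0.7 (df 23). A reader might conclude that the model gives clearly more power at no cost. The documents do not support this. The 1.6 SD is not the protocol's figure, the split of 32 by arm is not stated, and r is not given. At d = 0.8 and r of 0.2 or less the gain is only about 1 to 4 points. Against a change-score t-test with 16 per arm and r = 0.7 it is 0.81 to 0.88.

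**There is a cost.** The model needs a common residual variance and slope across three treatment sites. No benefit from the clinic terms can be quantified without a clinic effect size; the reason for them is to match the stratified randomisation. Both points stand.

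**Conclusion.** The point holds as a cheap improvement, not as an error that invalidates the trial. The sentence leaves the main comparison undefined, and a better method is available on data already collected. In every scenario tried, the six-arm model had at least the power of a t-test on final values or on changes. The gain is substantial at r of 0.5 or more and slight at r of 0.2 or less. These figures rest on assumed correlations, on reading 0.8 as a pairwise standardised difference, and on the assumed split of the 32; the 12% and 25% within-arm figures rest on an assumed drift.

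The model should not be taken to rescue the trial. If 32 is the total, power at d = 0.8 and r = 0.5 is still only about 0.27 to 0.30.

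**What to change.** In the Statistical analysis section, replace the t-test for IL-10, TNF-alpha and nitric oxide by one linear model per biomarker over all six arms: follow-up value on arm, baseline value and clinic.

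- Fix the scale in advance, for example log for skewed cytokines.
- Report three prespecified contrasts, active minus sham at the same site, with 95% confidence intervals.
- Analyse EDSS with an ordinal method, or justify treating it as continuous.
- State that within-arm before-after tests are descriptive only.

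The cost is a change of wording, with no added patients or visits, and the model runs in the planned software. It spends 1 df on baseline and 2 on clinic, and the common variance and slope should be checked. The sample size needs separate attention.

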Prognosis is unpredictable with regard to the disability that occurs due to the manifestations of the disease, which are normally associated with progressive locomotion impairment.[12] Treatment is directed at the immune response and slowing the progression of the disease, which can be achieved with the use of drugs.[12,13] Moreover, rehabilitation can lead to improvements in walking capacity, cognition, fatigue, depression, quality of life, participation in activities, muscle strength, cardiovascular performance, and balance.[13,14]

In vitro and in vivo studies have demonstrated that photobiomodulation is effective for inflammatory diseases, including MS.[15] This therapeutic modality has a broad range of benefits, such as the avoidance of cell and tissue death, the stimulation of healing and injury repair, reductions in pain, edema and inflammation, cell proliferation, and even apoptosis.[15,16] The outcomes of photobiomodulation include the regeneration of

cells, the stimulation of the growth of Schwann cells, a reduction in spasticity, functional improvements, a reduction in nitric oxide levels, and the upregulation of the cytokine IL10, demonstrating that this therapeutic modality can offer neuroprotection.[15,17]

The aim of the proposed study is to evaluate whether photobiomodulation in the sublingual region and along the spinal cord modulates the expression of IL-10, TNF- $\alpha$ , and nitric oxide in individuals with MS. The main objective of this study is to evaluate if the photobiomodulation along the spinal cord in the sublingual region and irradiation in the radial artery can modulate the expression of IL-10, TNF- $\alpha$ , and nitric oxide.

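### For six arms in a 3 (site) x 2 (active/sham) layout, the protocol names only a two-group t-test for continuous outcomes and no groups to compare; one six-arm model would use every patient

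*Protocol*

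**What the plan says.** **Layout.** The Abstract says "The patients will be divided into 6 groups". Recruitment and randomization lists three pairs. The first is sublingual: "Groups 1 and 2 will receive sham and active photobiomodulation in the sublingual region, respectively". The spinal site has the same sham/active pairing in arms 3 and 4. The third pair is radial, with this control arm: "Group 5 will receive placebo treatment with photobiomodulation on the skin in the region of the radial artery with a specific bracelet". Its active counterpart is arm 6. Allocation is equal: "Randomization will be stratified by clinic using block allocation tables to ensure equal proportions in the distribution of treatments".

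**Objective.** The Introduction asks for one set of markers (IL-10, TNF-alpha, nitric oxide) across the three sites: "evaluate if the photobiomodulation along the spinal cord in the sublingual region and irradiation in the radial artery can modulate the expression".

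**Analysis.** The Statistical analysis section says "The Student's t-test will be used and Pearson's correlation coefficients will be calculated for the analysis of correlations among the continuous variables". It gives chi-square and Fisher tests for categorical variables. It names no model with all arms and no contrast, and it does not say which groups enter the t-test.

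**Size.** The Sample calculation reports power of 0.9566 "with 32 individuals and an effect size of 0.8" at alpha 0.05. The text does not say which test this is for, what kind of effect size 0.8 is, or whether 32 is the whole trial. Figure 1, which may show this, is not in the text at hand.

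**The concern.** A t-test compares two groups, and the trial has six. The natural way to apply it is each active arm against the sham at the same site. Each comparison would then rest on about ten of the 32 patients. The other 22 or so would contribute nothing to it, not even to the estimate of residual variance. Half the patients would sit in three separate sham groups, each used once.

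The objective can be read as asking about photobiomodulation over all three sites or about each site in turn. The named test serves the second reading poorly and gives no answer to the first. Intervals from about 5 v 5 patients are so wide that a null result would say little. Three separate p-values also invite the conclusion that one site works and another does not, which they cannot support.

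**Working it through.** **Inputs.** Six arms with equal allocation (Abstract; Recruitment and randomization). N = 32, effect size 0.8, alpha 0.05, power 0.9566 (Sample calculation). Assumed: 32 is the trial total, tests are two-sided, there is no dropout, and there is no baseline or clinic adjustment. Then n = 32/6 = 5.33 per arm, in practice 5 or 6.

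**1. The stated power.** For a one-way ANOVA with Cohen's f = 0.8, the noncentrality is f²N = 0.64 x 32 = 20.48.
- Four groups (3 and 28 df): 0.9566, the stated figure.
- Six groups (5 and 26 df): 0.903.
- Two-sample t-test, 16 v 16, d = 0.8: 0.591.

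Of the calculations tried, only the four-group ANOVA with f = 0.8 reproduces 0.9566. For a common active-v-sham difference in equal groups f = d/2, so f = 0.8 means d = 1.6. Both d = 0.8 and d = 1.6 are carried forward.

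**2. Own-sham t-test.** SE = sqrt(2/5.33) = 0.612 SD; df = 2 x 5.33 - 2 = 8.67; critical t = 2.275. The 95% CI half-width is 0.612 x 2.275 = 1.39 SD. Power at d = 0.8 is 0.21 (0.20 at 5 v 5, 0.24 at 6 v 6).

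**3. Same contrast from a six-arm model.** The SE is the same, but residual df = 32 - 6 = 26 and critical t = 2.056. The half-width is 0.612 x 2.056 = 1.26 SD and power is 0.24. The gain is small and comes only from the shared residual variance.

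**4. Overall contrast**, the equally weighted mean of the three within-site differences. SE = sqrt(6/5.33)/3 = 0.354 SD; half-width 0.354 x 2.056 = 0.73 SD. The mean effect is 0.8 if all three sites respond, 2 x 0.8/3 = 0.533 if two do, and 0.8/3 = 0.267 if one does.

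**5. One active arm v the three shams combined.** SE = sqrt(1/5.33 + 1/16) = 0.500 SD. Power at d = 0.8 is 0.34.

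| Contrast | d = 0.8 | d = 1.6 |
|---|---|---|
| Own-sham t-test | 0.21 | 0.64 |
| Overall, three sites respond equally | 0.59 | 0.99 |
| Overall, two respond | 0.31 | 0.83 |
| Overall, one responds | 0.11 | 0.31 |

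When all three sites respond equally, the ratio of overall to own-sham power is 0.587/0.214 = 2.7 at d = 0.8 and 0.99/0.64, about 1.6, at d = 1.6. When only one site responds, the overall contrast does worse than that site's own pair at either effect size.

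**The case against.** **The pairing is inferred.** The protocol does not say that each active arm meets its own sham, nor that 32 is the total. A t-test of all active v all sham patients fits the wording too, and 16 v 16 at d = 0.8 already gives 0.59. The exact model is often left to an analysis plan, and one may exist. This stands as a limit on the claim. It does not remove the point, because the protocol does name a test, and that test alone does not determine how six arms are to be compared.

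**A reader might infer that combining the sites nearly triples the power.** The documents do not support that as a general statement. It needs 0.8 to be a standardised mean difference and the effect to be equal at all three sites. The stated 0.9566 points to Cohen's f, where the gain is about 1.6 times. Table 1 gives the spinal site about 180 J over 1800 s against about 36 J over 360 s at the other two, so equal effects are not a safe default.

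**Three uncorrected pairs are a fairer comparator.** At 0.05 each and d = 0.8, at least one pair is significant with probability 1 - 0.786³ = 0.51 if three sites respond, 1 - 0.786² x 0.95 = 0.41 if two do, and 1 - 0.786 x 0.95² = 0.29 if one does. The overall contrast (0.59, 0.31, 0.11) beats that only when all three respond. This is correct, but the uncorrected strategy has a familywise error of 1 - 0.95³ = 0.14, so the two are not on equal terms.

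**An average answers a different question.** It cannot say whether any one site works, and own-sham comparison is a legitimate choice for site-specific questions. This stands. The documents give no ground for saying that the average must lead or that the objective must be reworded.

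**Sham arms may differ.** The protocol does not describe how sham is delivered, so a common sham mean is an assumption. This is why the combined-sham comparison can only be supportive.

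**Conclusion.** The point holds as a modest, nearly free improvement. The protocol names a two-group test for a six-arm layout and leaves the groups unspecified. Applied pair by pair to 32 patients, that test gives about 5 v 5, a half-width of 1.39 SD and 21% power at d = 0.8 (64% at d = 1.6).

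A six-arm model keeps every site-specific contrast and makes it slightly more precise (1.26 SD, 24% at d = 0.8). It adds an overall contrast with a half-width of 0.73 SD. Against a single own-sham pair, that contrast gains power only when at least two sites respond, and it loses when only one does.

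A reader might also infer that combining arms rescues the sample size. At d = 0.8 it does not: 59% is far below the planned 95%. At d = 1.6 the overall contrast passes 95% only on the assumption of equal effects at all sites. That 0.9566 matches a four-group ANOVA while the trial has six arms and the analysis names a t-test is a separate inconsistency to reconcile.

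All figures rest on 32 as the total, two-sided 0.05, no dropout and no covariate adjustment.

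**What to change.** In Statistical analysis, for each of IL-10, TNF-alpha and nitric oxide:

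1. Fit one model with all six arms.
2. Report the three within-site active-minus-sham differences with 95% CIs from that model. The site-specific questions in the Introduction stay as they are.
3. Add a prespecified overall contrast, the equally weighted mean of those three differences. Each site keeps its own sham, so the comparison remains randomised.
4. As a supportive analysis, compare each active arm with the three shams combined, stating the assumption of a common sham mean.
5. Do not conclude that sites differ because one p-value is below 0.05 and another is not.
6. State in advance whether the overall or the site-specific contrast leads. That is the sponsor's choice.

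The cost is wording, with no extra patients, visits or assays. The downsides should be stated alongside: the overall contrast averages regimens that differ in energy (180 J v 36 J) and is diluted if only one site works, and the supportive analysis is biased if the sham arms do not share a mean.
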